## Methods/Design

### Study Design

The present study is a 2-arm (telephone counselling versus control condition) randomized controlled trial with three assessments during a period of approximately one year. Participants will be 512 smoking parents and their 9-12 year old children. After giving informed consent and after completing the baseline assessment, 256 parents will be randomly assigned to the telephone counselling condition and 256 parents to the control condition. In the telephone counselling condition, parents will receive up to seven counsellor-initiated telephone calls and three supplementary brochures over a period of approximately three months. In the control condition, parents will receive a standard brochure on smoking cessation. Parent and child assessments will be identical across conditions and take place at baseline, three months after start of the intervention (post-measurement), and twelve months after start of the intervention (follow-up measurement). In both conditions, each parent-child couple will receive an incentive of 100 euro for their participation in all assessments.

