### Sample size calculation

Based on similar studies, we expected a 6% difference in 7-day point prevalence abstinence rates between the telephone counselling condition and the control condition at 12-months assessment (13% versus 7%, respectively). A statistical power of .80 was targeted. Hypotheses will be tested at a two-sided significance level of .05. The calculated sample size was corrected for participants who will be lost to attrition. Additionally, the sample size was corrected to allow for supplementary analyses of mediation and moderation.

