### Outcomes

In the proposed study, telephone counselling aims to increase cessation rates among smoking parents. The primary outcome measures will be: 1) sustained abstinence between post-measurement and follow-up measurement, 2) 7-day point prevalence abstinence at post-measurement (three months post-intervention) and follow-up measurement (twelve months post-intervention), and 3) 24-hours point prevalence abstinence at post-measurement and follow-up measurement. Additionally, biochemical validation of self-reported smoking cessation will be reported for a random sample (30%) of all study participants who report 7-day point prevalence at follow-up assessment, thereby allowing to estimate the occurrence of over-reporting of abstinence. Secondary outcome measures will include: a 50% reduction in the number of cigarettes smoked per day, occurrence of abstinence of at least 24 hours at some point during the study, implementation of smoking restrictions at home, increase in motivation to quit, use of and adherence to nicotine replacement therapy, number and duration of quit attempts, and change in smoking-related cognitions (e.g., attitudes towards smoking, self-efficacy, social norms). In addition, secondary outcomes will include smoking-related cognitions of children (e.g., attitudes towards smoking, self-efficacy, social norms, intention to smoke) and smoking behaviour of children.

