### Statistical analyses

Analyses will be conducted to check whether the randomization has resulted in an equal baseline distribution of relevant participant characteristics across both conditions. In case of group differences at baseline, confounding variables will be included in subsequent analyses. To evaluate smoking cessation rates across groups, we will use logistic regression models. Effect sizes as well as confidence intervals will be reported. To evaluate smoking-related cognitions across groups (in both parents and children), analyses-of-variance and regression analyses will be used. Mediation and moderation will be tested in Mplus. In accordance with the intent-to-treat principle, all participants randomized to a condition will be included in analyses testing of the study hypotheses. In addition, a complete-case analysis will also be conducted, that is, only participants with outcome data on all assessments will be included in the analysis.

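### The supplementary complete-case analysis requires data at every assessment, so it drops point-prevalence outcomes that were observed (minor)

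*Protocol article*

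**What the plan says.** The Statistical analyses section sets up two analyses. In the first, under the intent-to-treat principle, "all participants randomized to a condition will be included in analyses testing of the study hypotheses". The second is supplementary: "In addition, a complete-case analysis will also be conducted", and it is defined by the rule that "only participants with outcome data on all assessments will be included in the analysis".

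The Study Design section lists the assessments as "baseline, three months after start of the intervention (post-measurement), and twelve months after start of the intervention (follow-up measurement"). It places randomisation "After giving informed consent and after completing the baseline assessment", so in practice the rule means data at both follow-ups.

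The Outcomes section names three kinds of primary outcome. One spans the two follow-ups: "sustained abstinence between post-measurement and follow-up measurement". The second is "7-day point prevalence abstinence at post-measurement (three months post-intervention) and follow-up measurement (twelve months post-intervention"), and the third is 24-hour abstinence at the same two times. That makes five comparisons, four of them tied to a single follow-up. Months 3 and 12 below are counted as in the Study Design section.

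**The concern.** The rule fits sustained abstinence, which runs from one follow-up to the other. For the other four comparisons it asks for data that the outcome does not need, with two consequences that follow from the definition alone:

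- At month 12, a parent with a valid answer is left out because the month-3 form is missing.
- At month 3, a parent with a valid answer is left out because of non-response nine months later. Membership of the 3-month set then depends on something that happens after the outcome, and that relapse could influence.

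Any analysis of observed data selects on having the outcome. This rule adds a second filter, attendance at a different assessment, which serves no purpose for a single-time-point outcome. At stake is the value of the supplementary analysis as a check on the all-randomised result. It is less precise than the collected data allow, and a difference between the two results would reflect missing outcomes mixed with discarded ones.

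**Working it through.** The plan gives no figure for missing data or for the size of the complete-case set, so there is none to reproduce. The Sample size calculation section says attrition was allowed for but gives no rate.

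**Inputs.** N = 512 randomised (Study Design section). Assumed, not from the documents: a fraction m missing at each follow-up, the same at both, with m from 0.10 to 0.20.

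**Available at month 12:** 512 × (1 − m).
- m = 0.10: 460.8, about 461
- m = 0.20: 409.6, about 410

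**Passing the all-assessments rule**, by how far the two groups of non-responders overlap:
- Full overlap (the same parents miss both): 512 × (1 − m), so nothing is lost.
- Half overlap (half of the month-12 non-responders also missed month 3): 512 × (1 − m − m/2).
- Independent: 512 × (1 − m)².

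**Standard error.** At equal event rates it scales with 1/√n, so the ratio is √(available / passing).

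| Overlap | m | Available at 12 months | Pass the rule | 12-month outcomes lost | SE ratio |
|---|---|---|---|---|---|
| Full | 0.10 | 460.8 | 460.8 | 0 | 1.00 |
| Full | 0.20 | 409.6 | 409.6 | 0 | 1.00 |
| Half | 0.10 | 460.8 | 435.2 | 25.6 (26) | √(460.8/435.2) = 1.03 |
| Half | 0.20 | 409.6 | 358.4 | 51.2 (51) | √(409.6/358.4) = 1.07 |
| Independent | 0.10 | 460.8 | 414.7 | 46.1 (46) | √(1/0.9) = 1.05 |
| Independent | 0.20 | 409.6 | 327.7 | 81.9 (82) | √(1/0.8) = 1.12 |

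**Month 3.** With equal missingness at both follow-ups, the same counts of 3-month outcomes are lost. If missingness grows over time, 3-month answers are lost even when every month-3 non-responder also misses month 12. With 10% missing at month 3 and 20% at month 12, that is 512 × (0.20 − 0.10) = 51.2, about 51.

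**When the extra filter adds bias.** Among parents with the outcome observed, let q be the probability of also attending the other follow-up, by arm (1 counselling, 0 control) and by status at the outcome's time point (A abstinent, S smoking). The filter multiplies the unadjusted odds ratio, the scale of the planned logistic regression, by

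(q1A × q0S) / (q1S × q0A).

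This equals 1 when attendance depends on smoking status in the same proportion in both arms. It differs from 1 only when that dependence differs by arm. The documents supply none of the four probabilities, so neither the direction nor the size can be computed.

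**The case against.** The strongest reply is that no hypothesis test rests on this rule. The article assigns those tests to the all-randomised analysis and introduces the complete-case analysis as an addition. Nothing in it lets the second result replace the first. This stands and sets the priority. A reader might infer that the trial's main comparison is biased or loses participants, but the documents do not support that.

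A second reply is that selection on attendance is common to all observed-data analyses, including the one proposed below. That also stands. Only the extra filter counts against the rule, and it removes no 12-month outcome if all month-3 non-responders are missing at month 12 too.

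A third is that one fixed set of completers is a recognised definition. It suits sustained abstinence and keeps the same parents in every comparison. This is a fair preference, but a weak reason to discard observed primary outcomes.

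Three stronger readings are tempting and should be resisted:

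- **A numerical bias.** Take the planned rates ("13% versus 7%, respectively") and assume that 3-month forms come back from 95% of quitters in both arms, from 75% to 80% of continuing smokers under counselling and from 90% in control. The 12-month difference then becomes 7.7 to 8.6 points instead of 6. This is not the effect of the rule. The 6 points presuppose complete 12-month data. If 12-month response followed the same pattern, the per-outcome analysis would show the same inflation. The example also lets 12-month status govern return of a form due nine months earlier, and its response rates have no source in the documents.
- **An uninterpretable disagreement.** Counts of respondents at each assessment would show how many parents were excluded only for the other follow-up.
- **The trial's sole missing-data check.** It is the only one the article states, but a condensed article may leave others to the full protocol or analysis plan.

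**Conclusion.** The point holds as a minor flaw in a supplementary analysis. The article fixes a completeness rule that does not match four of its five primary comparisons, and so excludes outcomes that were observed. That much follows from the text without any assumption.

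The size does rest on assumptions: equal missingness of 10% to 20% at each follow-up and a given degree of overlap. Over that range the loss runs from none to 82 of 512 twelve-month outcomes, and the supplementary standard error from unchanged to 12% wider. Added bias in the odds ratio is possible only where attendance depends on smoking status differently by arm, and no figure should be put on it from these documents. The all-randomised analysis is untouched.

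**What to change.** Replace the complete-case sentence with a rule per outcome and time point. For example: *As a sensitivity analysis, each point-prevalence outcome will be analysed in every randomised parent for whom that outcome was observed at that time point. For sustained abstinence, data at both follow-ups are required. The number analysed will be reported for each outcome.*

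This is a change of wording that needs no new data. The downside is that the number analysed, and the parents who make it up, will differ between outcomes, so each row of the results table has to show its own N.

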## Discussion

The present study protocol presents the design of a randomized controlled trial evaluating the effectiveness of proactive telephone counselling in smoking parents. The purpose of telephone counselling is to increase smoking cessation rates among parents. We hypothesize that cessation rates will be higher in the telephone counselling condition compared to the control condition, both at three-months post-measurement as well as twelve-months follow-up measurement. Additionally, we hypothesize that children of parents receiving telephone counselling will have more negative attitudes towards smoking, perceive stronger social norms against smoking, have higher self-efficacy to refrain from smoking, and have a lower intention to start smoking than will children of parents in the control condition.

### Strengths and limitations

Strengths of the study include a 12-month follow-up assessment, which meets smoking cessation research recommendations [20]. A limitation of the study is that smoking cessation will be assessed by self-report. However, the present study counteracts reporting biases by informing participants that a random sample of participants will be asked for biochemical validation of self-reported smoking cessation. Biochemical validation of self-reported smoking cessation will be reported for a subsample (30%) of all study participants who report 7-day point prevalence at follow-up assessment, thereby allowing to correct for over-reporting of abstinence. Another potential limitation is that the impact of the intervention on children's cognitions about smoking may be limited by the degree to which their parents quit smoking.

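### Testing 30% of self-reported quitters gives about 15 samples (about 10 versus 5 by arm): enough for a rough description of over-reporting, not for the correction the Discussion claims

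*Protocol article*

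**What the plan says.** The Outcomes section of the protocol article makes self-reported abstinence primary, and adds that "biochemical validation of self-reported smoking cessation will be reported for a random sample (30%) of all study participants" who report 7-day abstinence at the follow-up assessment. It gives the purpose as "thereby allowing to estimate the occurrence of over-reporting of abstinence".

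The Strengths and limitations section names self-report as a limitation and offers two safeguards. Participants are told that a random sample will be asked for biochemical validation, and the same 30% subsample is described as "thereby allowing to correct for over-reporting of abstinence".

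The Statistical analyses section plans logistic regression for cessation rates and describes no correction step. No expected number of validation samples is given. The arm sizes are in Study Design ("256 parents will be randomly assigned to the telephone counselling condition and 256 parents to the control condition"). The expected 7-day abstinence rates at 12 months are in Sample size calculation ("13% versus 7%, respectively", counselling first).

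**The concern.** One subsample is given two different purposes. Estimating how often abstinence is over-reported is a modest aim. Correcting the abstinence result for it is a stronger property, and it is offered as an answer to the trial's main measurement weakness.

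A correction of the treatment comparison needs the over-reporting rate in each arm, or good grounds for treating the two rates as equal. Parents know whether they have had up to seven counselling calls or a brochure, so unequal over-reporting is plausible. If over-reporting were, for illustration, 30% with counselling and 10% in control, the self-reported 13% versus 7% would become 13% × 0.70 = 9.1% versus 7% × 0.90 = 6.3%. A 6-point difference would shrink to 2.8 points. A reader told that the design can correct for this would be reassured about the primary outcome without basis, unless the subsample is large enough to do it.

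**Working it through.** **Inputs.** From Study Design: 256 per arm. From Sample size calculation: 13% and 7%. From Outcomes: a 30% validation fraction. Assumed, because the article gives no figures: the proportion failing validation (20%, with 0% also shown) and attrition (0% to 30%).

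**The plan's own figure.** The article states no number of validation samples, so there is none to reproduce. The total of 512 does not follow from its stated inputs. With the pooled formula at 80% power and two-sided 5%, n = [1.96 × √(2 × 0.10 × 0.90) + 0.842 × √(0.13 × 0.87 + 0.07 × 0.93)]² / 0.06² ≈ 392 per arm. That is a separate matter, and this point does not depend on it: at 392 per arm the subsample would be 0.30 × (51.0 + 27.4) ≈ 24, about 15 and 8.

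**Step 1. Number of tests.**
- Self-reported quitters: 256 × 0.13 = 33.3 and 256 × 0.07 = 17.9, total 51.2.
- Tested: 0.30 × 33.3 = 10.0 and 0.30 × 17.9 = 5.4, total 15.4.
- If the rates apply only to parents followed up, 20% loss gives 8.0 + 4.3 = 12.3 tests, and 30% loss gives 7.0 + 3.8 = 10.8.

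**Step 2. Precision of the over-reporting rate** (exact Clopper-Pearson 95% intervals).

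| Sample | About 20% fail | None fail (upper limit) |
|---|---|---|
| Pooled, n = 15 | 3/15: 4% to 48% | 22% |
| Counselling, n = 10 | 2/10: 3% to 56% | 31% |
| Control, n = 5 | 1/5: 0.5% to 72% | 52% |

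**Step 3. Pooled correction.** Both rates are multiplied by (1 − m), where m is the pooled over-reporting rate. Over the interval for 3/15, the 6-point difference becomes 6 × (1 − 0.481) = 3.1 to 6 × (1 − 0.043) = 5.7 points. The risk ratio stays at 13/7 whatever m is, so a pooled correction cannot remove a bias that differs between arms.

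**Step 4. Arm-specific correction.** Take 20% over-reporting in both arms and hold the quit rates fixed. The corrected difference is 0.80 × 6 = 4.8 points. The standard deviation added by the validation sample is:
- Counselling: 13 × √(0.2 × 0.8 / 10) = 1.64 points.
- Control: 7 × √(0.2 × 0.8 / 5) = 1.25 points.
- Difference: √(1.64² + 1.25²) = 2.07 points.

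The 95% range is 4.8 ± 1.96 × 2.07, or about 0.8 to 8.8 points, a width of about 8 points. One failed test among five controls alone moves the control rate by 7 × 1/5 = 1.4 points.

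**Step 5. Can equal over-reporting be checked?** With 10 and 5 tests, the power of Fisher's exact test (two-sided 5%) is about 3% for 30% versus 10%, and about 17% for 40% versus 0%.

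**Step 6. Balance of the draw.** If 15 were drawn at random from 51 quitters (33 and 18) without regard to arm, the chance of three or fewer control tests would be 12% (hypergeometric).

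**The case against.** The strongest defence is that nothing planned depends on the disputed words. They stand in the Discussion. The Outcomes section promises only an estimate, and the Statistical analyses section contains no correction. A reader might infer that a corrected effect will replace the self-reported one; the article does not say so. This stands, and it limits the point to a property claimed for the design.

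A reader might also infer that any correction from 15 samples would move the treatment effect by more than the effect itself. That is not so for a pooled correction, which moves the difference by 5.7 − 3.1 = 2.6 points, without a change of sign. It is true only of the width of the arm-specific range in Step 4. Even there, with all sampling error counted, simulation gives a standard deviation of about 2.9 points, against 2.6 for the uncorrected difference, so the added noise is moderate.

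Nor does the article show that counselled parents over-report more. The 30% versus 10% case and the 20% failure rate are illustrations. Telling participants about validation may deter misreporting however few samples are tested. The article does not say whether the draw is stratified by arm, and a condensed article may leave that to a fuller document.

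These objections narrow the point but do not remove it. No fuller document can make 30% of about 51 people larger. Testing every quitter (about 33 and 18) would give only about 28% power for 30% versus 10%, so the remedy is a weaker claim with a sensitivity analysis.

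**Conclusion.** The concern holds as a limited one. Under the plan's own rates and arm sizes, about 15 tests (about 10 and 5) can support a rough description of over-reporting, which is what the Outcomes section claims. They cannot support the correction claimed in Strengths and limitations. A pooled correction has to assume what is in doubt, and an arm-specific one is too imprecise, with a range about 8 points wide around 4.8.

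The count follows directly from the article's figures and is near the upper end under those rates, because attrition lowers it. The intervals depend on the assumed number of failed tests; in the most favourable case, no failures in 15, over-reporting of up to about 22% is still not excluded. The conclusion does not rest on differential over-reporting being present, only on the subsample's inability to detect it or adjust for it.

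**What to change.** - Bring Strengths and limitations into line with Outcomes: the subsample allows over-reporting to be estimated, not corrected for.
- Draw the 30% separately within each arm. This barely changes precision, but it prevents a chance shortage of control tests.
- Report over-reporting by arm with exact confidence intervals, labelled as descriptive.
- Add a sensitivity (tipping-point) table of the 12-month abstinence effect over a grid of arm-specific over-reporting rates, for example 0% to 50% in each arm, so that readers can see how unequal reporting would have to be to change the conclusion.

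The cost is a weaker claimed strength, a stratified draw and one additional table. No extra biochemical tests are needed.

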### Implications for practice

Results of the present study can be of help in adapting telephone counselling and in tailoring telephone counselling to the needs of particular subgroups. If the intervention is found effective, it can be advertised through schools to reach the population of smoking parents. If children are found to benefit from this intervention, proactive recruitment of smoking parents into telephone counselling may be incorporated in national prevention campaigns, such as the "Healthy School and Drugs" program [21], which has already been implemented in numerous schools, institutions, and treatment facilities.

## Conclusions

The proposed study will evaluate the effectiveness of proactive telephone counselling to aid smoking cessation among smoking parents. Additionally, it will evaluate whether children of smoking parents receiving telephone counselling have less favorable cognitions about smoking than do children of parents in the control condition. The results of this study will provide insight into parent characteristics and intervention characteristics associated with successful smoking cessation. In addition, the proposed study will provide insight into the intergenerational transmission of smoking-related cognitions as well as the associates and antecedents of favorable smoking-related cognitions in preadolescents.
